### Trial design {8}

This is a batched stepped wedge, comparative effectiveness, cluster randomised trial [13]. Participating sites will start the study in three batches; data collection in each batch starts 2 months after the start of the previous batch. Note that study power is unaffected by the exact timing of the start of each successive batch [13]. In each batch, hospitals will be randomised to the sequences of a five-sequence stepped wedge design, as indicated in Table 2. Initially all hospitals will continue to use their current standard radiology reporting (the comparator) for a period of between 6 and 30 months. In each batch, after each 6-month period, a randomly allocated group of hospitals will commence using the synoptic report template (the intervention), until all hospitals are using the synoptic report.

**Table 2 Tab2:**
[figure not shown]
Batched stepped wedge cluster randomised design—standard (represented as “0”) vs Synoptic Reports (represented as “1” in purple)

## Methods: participants, interventions, and outcomes

### Study setting {9}

The trial will be based at 33 Australian hospitals. A list of participating hospitals can be found via the following weblink in the ANZCTR: https://www.anzctr.org.au/ACTRN12623000508673.aspx.

Participating sites will provide data from eligible patients over the 36-month data collection period, with the first batch’s data collection period starting from July 2023.

### Eligibility criteria {10}

#### Inclusion criteria

The unit of randomisation here is the hospital. Hospitals are randomised at the time they commence synoptic reporting. The hospitals participating in the study must satisfy the following requirements:Hold a multi-disciplinary team meeting (MDM) where PDAC cases are presented;Are prepared for radiology reporting methods to be randomised;Manage on average ≥ 20 patients with PDAC annually (across all stages), andAre not currently using a synoptic radiological report for pancreatic cancer.

Each participating hospital will be providing access to relevant information of their patients with pancreatic cancer. Once presented to an MDM, follow-up data will be collected on all patients presented at the MDM, provided the patients are:Aged 18 years of age or older;Have suspected or proven adenocarcinoma of the pancreas; andHave an abdominal CT scan (either performed by hospital radiology departments or an external radiology service) as a part of standard clinical care for diagnostic purposes

#### Exclusion criteria

Patients with neuroendocrine tumours will be excluded from the study. No inclusion waivers will be allowed.

### Who will take informed consent? {26a}

Not applicable. Individual patient consent is not required. A waiver of consent has been granted by the Monash Health Human Research Ethics Committee (HREC).

### Additional consent provisions for collection and use of participant data and biological specimens {26b}

Not applicable. A waiver of consent has been granted by the Monash Health HREC. No biological specimens will be used*.*

## Interventions

### Explanation for the choice of comparators {6b}

#### Control group

The comparator for this study is continued use of the baseline standard radiology reporting process (i.e. standard reporting) at each of the participating sites (prior to the commencement of synoptic reporting).

Current standard radiology reporting varies, with the level of detail and the style of the report being radiologist dependent. The report is typically dictated by radiologists reviewing scans and usually written as a narrative of varying lengths and complexity, finishing with a conclusion. We will accurately document the current standard reporting process, and later compare it with the synoptic reporting template that is under study.

### Intervention description {11a}

#### Experimental group

After a site commences the use of synoptic radiology reporting (i.e. synoptic reporting), the site radiologist reviewing CT scans will use a structured reporting tool that was developed in the pilot study [12] to describe the patient’s pancreatic lesion in detail. The synoptic report template collects 63 discrete fields of data that concisely describe the pancreatic cancer mass characteristics, blood vessel, and other adjacent structure involvement, and determines the extent of local disease spread. The radiologist will assess a patient’s resectability status (based on the international consensus guidelines) by completing the synoptic report in a Research Electronic Data Capture (REDCap) application. The synoptic reporting template has been previously described [12]. The median time needed to complete a synoptic report for a patient by a radiologist during the pilot study was 4 min, so it is assumed the time will be similar for this study.

### Criteria for discontinuing or modifying allocated interventions {11b}

Not applicable. As mentioned above, after a site commences synoptic reporting, all the site radiologist/s will be reporting the CT scans using synoptic reporting rather than standard reporting. For trial patients, there is no “intervention” as such that any of them would need to discontinue.

### Strategies to improve adherence to interventions {11c}

Training will be provided to the sites’ radiologists by a project data manager and an experienced radiologist who has previously used the synoptic reporting tool. The training session will be delivered online and it will take about 30 min to complete. Training will commence 1 month prior to the start of the synoptic reporting phase of a sites’ participation.

To monitor adherence to the synoptic reporting tool, the data manager in the central project team will ensure data completeness and accuracy by undertaking quality assurance checks and ensuring ongoing training and support to participating radiologists is available.

### Relevant concomitant care permitted or prohibited during the trial {11d}

Not relevant, this study relates only to the discussion and planning phase of treatment and there will be no impact on concomitant or future care subsequent to the MDM presentation.

### Provisions for post-trial care {30}

Not relevant. This study relates only to the discussion and planning phase of treatment.

### Outcomes {12}

The primary outcome is the proportion of patients diagnosed with BR PDAC, aiming to detect a change in this proportion before and after introduction of the synoptic report. There are a number of secondary outcomes (see Table 1).

### Participant timeline {13}

After obtaining site governance authorisation, randomisation, and sequence allocation (Fig. 2), all patients who undergo presentation of radiological staging of PDAC at each participating institution MDM will be included in the study, and their baseline data and subsequent data will be collected as per the descriptions in Table 3.

**Fig. 2 Fig2:**
[figure not shown]
SPIRIT figure—Schedule of enrolment, interventions, and assessments of SCANPatient clinical trial**.** This is a batched, stepped wedge cluster randomised trial, more details of randomisation and sequencing can be found in Table 2. **For more details about timepoints for hospital allocation, please see Table 2

**Table 3 Tab3:** Data required, sources, methods and time to collect them^a^

What data and information are needed	Main sources and methods to collect/extract data	When to collect (Timepoint)		
		Baseline (diagnostic phase)^b^	Post-operative	12 and 24 months
Patient demographics, i.e. given name^c^, surname^c^, date of birth^c^, age, sex	MDM Report and radiology report, provided by participating radiologists or site focal point of contacts; extracted and enter into REDCap database by SCANPatient Project team	**✔**		
Health status, medical history, comorbidities, tumour markers (Ca19-9)	As above	**✔**		
Anatomical and overall resectability status (i.e. clearly resectable (CR), borderline resectable (BR), locally advanced (LA), or metastatic cancer)	As above	**✔**	**✔**	
CT scans, MRI scan, other diagnostic procedures *(As repeated per patient)*	As above	**✔**		
Other clinical data—Treatment plans/ management strategy and details, e.g. use of chemotherapy, radiology, best supportive care, and other forms of ca treatment	As above	**✔**	**✔**	
Operative intervention (surgical resection details, whether completed or abandoned, blood loss and other relevant operation details)	Surgical operation report, provided by participating surgeons, or site contacts; extracted by SCANPatient Project team		**✔**	
Histopathological outcome (resected tumour details, surgical resection margin assessment, lymph nodes, TNM staging, and other relevant histopathological details)	Pathology report of operation specimen, provided by participating surgeons, or site contacts; extracted by SCANPatient Project team		**✔**	
Outcome data, tumour recurrence, vital status (i.e. alive, dead, unknown, or lost to follow-up) and survival	As above; Data linkage to allow assessment of overall survival: link to AIHW Death Registry or to individual state death registries at the end of study; other possible death checks	**✔**	**✔**	**✔**
Radiological synoptic report fields of data^d^ (CT scan focused, after switching to synoptic reporting) • Quality assurance characteristics • Basic details • Distant metastases • Mass characteristics • Arterial evaluation • Venous evaluation • Conclusion and resectability status	Complete online (via central REDCap database) by radiologists from those sites that have been randomised to synoptic reporting		**✔**	**✔**
Clinician satisfaction data	Participating radiologists and hepatobiliary surgeons will be asked to complete an online survey using REDCap or Qualtrics at two time points to assess clinician satisfaction. The survey is developed by the project team (see Appendix 1). Responses to the survey are anonymised		**(**The first timepoint to assess clinician satisfaction is prior to site randomisation to synoptic reporting)	**(**The second timepoint is 6 months after randomisation to synoptic reporting)

*MDM* multi-disciplinary team meeting

^a^No additional investigations beyond standard care or follow-up information outside of routine audit will be required or collected

^b^Some data present at baseline will be collected over the ensuing 3–6 months from health records

^c^Identifiable data per site approval

^d^There are around 60 discrete fields of data in the synoptic reporting template

### Sample size {14}

Currently 8% of all patients diagnosed with PDAC are categorised with BR disease in the Upper Gastrointestinal Cancer Registry (UGICR; unpublished data) which is operating in most major centres in Victoria and approximately half of the major centres in New South Wales. We hypothesise that with the introduction of a new structured radiology report, leading to increased diagnostic accuracy, this will increase to 15%. This is supported by the final results of the pilot synoptic report study (wherein the rate of BR disease was 13% in the pilot study across 95 patients [12]) and international registry data which have shown that the rate of resection of major vascular structures at the time of surgery for PDAC is between 10 and 15% [14], a surrogate for involvement of those major structures and therefore a pseudo-definition of BR disease. As not all patients with BR PDAC will require formal venous or arterial resection, it is likely the actual rate of BR disease is higher in these larger international and national registries. An increase in the diagnosed rate of BR disease to this level will result in more patients appropriately being given neoadjuvant therapy, and a clinically meaningful change in the standard of care if identified.

The trial was originally designed as a standard, stepped wedge design with 8 hospitals randomised to each sequence of a standard 5-sequence/6-period stepped wedge design (a total of 40 hospitals). With 15 patients per hospital in each 6-month period, assuming a two-sided significance level of 0.05, this design has power ≥ 80% to detect an increase from 8 to 15% in the primary outcome. Power is maintained for a wide range of intracluster correlations and alternative within-cluster correlation structures, e.g. for a discrete time decay within-cluster correlation structure [15], with an intracluster correlation of 0.1 and a cluster autocorrelation of 0.55, power is 84%. Under most within-cluster correlation structure assumptions, power will remain > 76% should hospital recruitment be up to 25% lower and patient recruitment up to 30% lower than expected (i.e. with 10 patients each year in each of 30 hospitals). With the batched variant shown in Table 2, for the extreme scenario considered above (an intracluster correlation of 0.1 and cluster autocorrelation of 0.55), power levels remain > 80%. Sample size calculations were performed using the Shiny CRT calculator [16].

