## Trial status

The most updated protocol version is Protocol V1.3, 3 November 2023. Recruitment started in July 2023 in the first batch of 12 trial sites. The second batch then started in the 10 sites in September, and the third and final batch of 11 sites in November of 2023. Recruitment will be completed in about September 2026.

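### The power above 80% stated for the batched design gives no hospital count; at the protocol's own inputs the 33 hospitals in the trial give about 76%

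*Protocol article*

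**What the plan says.** All references are to the protocol article.

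- **Sample size {14}, original design.** The trial was first planned with "8 hospitals randomised to each sequence of a standard 5-sequence/6-period stepped wedge design (a total of 40 hospitals"). The inputs are "With 15 patients per hospital in each 6-month period", "assuming a two-sided significance level of 0.05", and power "to detect an increase from 8 to 15% in the primary outcome". For a discrete-time decay correlation structure the section reports: "with an intracluster correlation of 0.1 and a cluster autocorrelation of 0.55, power is 84" per cent.
- **Sample size {14}, current design.** The section then turns to the batched version: "With the batched variant shown in Table 2, for the extreme scenario considered above (an intracluster correlation of 0.1 and cluster autocorrelation of 0.55"). For that case it states power above 80%. It gives no hospital count and no cluster-period size for this figure.
- **Study setting {9}.** "The trial will be based at 33 Australian hospitals".
- **Trial status.** "Recruitment started in July 2023 in the first batch of 12 trial sites"; the second and third batches have 10 and 11 sites.
- **Trial design {8} and Statistical methods {20a}.** Each batch uses five sequences. The model has discrete-time decay within clusters and its own set of period effects for each batch.
- **Abstract, Methods.** The total is 2400 patients, with 36 months of data collection per batch.

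**The concern.** The batched-variant sentence is the only power statement for the design being run. It carries over the correlation values of the 40-hospital calculation, and a reader will naturally carry over the other inputs too. But the article fixes the trial at 12 + 10 + 11 = 33 hospitals, seven fewer than the 40 behind the 84%. In a stepped wedge with a given cluster-period size, the information on the treatment effect is roughly proportional to the number of clusters, so power should drop visibly. The question is whether it drops below the stated 80%.

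At stake is the accuracy of the prospective power statement for the primary outcome, in the scenario that the protocol puts forward to show that its design is robust.

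**Working it through.** **Inputs, all from the protocol article.** Rates 8% and 15% (difference 0.07); two-sided 5%; m = 15 patients per hospital-period; T = 6 periods and 5 sequences; ICC 0.1; cluster autocorrelation (CAC) 0.55 with discrete-time decay; period effects separate for each batch.

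**Method.** Generalised least squares on cluster-period means.

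- Outcome variance: s² = [0.08 × 0.92 + 0.15 × 0.85] / 2 = (0.0736 + 0.1275) / 2 = 0.10055.
- Covariance of one hospital's six period means: V(t, t′) = s² [ICC × CAC^|t − t′| + 1(t = t′) × (1 − ICC)/m].
- For each batch, sum Z′V⁻¹Z over its hospitals, where Z holds six period indicators and the treatment indicator. The information on treatment is the reciprocal of the treatment element of the inverse. Because each batch has its own period effects, information adds across batches.
- SE = 1/√information; power = Φ(0.07/SE − 1.96).

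**Step 1: reproduce the protocol's figure.** 40 hospitals, 8 per sequence, m = 15: information 1776.9, SE 0.02372, 0.07/SE = 2.951, power Φ(0.991) = 83.9%, against 84% stated. The formula is therefore the right one to carry forward.

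**Step 2: does batching cost power?** 40 hospitals split 15/15/10 (3, 3 and 2 per sequence) give 83.9% again. Batching alone costs nothing.

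**Step 3: the 33 hospitals.** The number per sequence is not visible, so a near-balanced allocation is assumed: 3,3,2,2,2 / 2,2,2,2,2 / 3,2,2,2,2.

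- Information: 529.6 + 444.2 + 495.2 = 1469.0.
- SE = 0.02609; 0.07/SE = 2.683; power = Φ(0.723) = 76.5%.

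Over every allocation of 12/10/11 with at least two hospitals per sequence, power runs from 75.0% to 77.1%. With at least one per sequence, the maximum is 78.3%.

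**Step 4: what would reach 80% in this scenario.**

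| Change, other inputs fixed | Power |
|---|---|
| 36 hospitals, m = 15 | 79.9% |
| 37 hospitals, m = 15 | 81.0% |
| 33 hospitals, m = 19 | 80.3% |

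**Step 5: the abstract's total.** 33 hospitals × 6 periods × 15 = 2970 patients, not 2400. A total of 2400 means 2400/198 = 12.1 per hospital-period, and power is then 72.6%.

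**Step 6: where 80% holds with 33 hospitals at m = 15.**

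| ICC | CAC | Power |
|---|---|---|
| 0.1 | 0.55 | 76.5% |
| 0.1 | 0.7 | 80.2% |
| 0.1 | 0.8 | 84.3% |
| 0.084 | 0.55 | 80.1% |
| 0.07 | 0.55 | 83.5% |
| 0.05 | 0.55 | 88.5% |
| 0.02 | 0.55 | 95.9% |

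**The case against.** **Table 2 cannot be seen.** The figure above 80% is tied to that table, whose content is missing from the text available. If it was computed for a batched layout of 37 or more hospitals, it was correct for that layout. This stands, and it limits the conclusion. A reader might infer that the protocol's power claim is simply false; the documents do not support that, because the hospital count behind it is not stated. What remains is that the article gives no count other than 33 for the batched trial, and 33 does not deliver the figure.

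**Another model might rescue it.** Block-exchangeable correlation gives 82.6% for 33 hospitals, but 89.0% for 40, so it cannot be the source of the 84%. The section also ties the scenario to discrete-time decay. Calendar-time effects shared across batches, which the protocol does not specify, give 79.3%.

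**Lower power is already disclosed.** The same section expects power above 76% with about 30 hospitals and fewer patients, under most correlation structures. That warns the reader in part, but it does not cover every structure and does not qualify the later sentence, which names one scenario and claims more than 80% for it.

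**The scenario is extreme and the gap is small.** Both are true. The difference detectable with 80% power moves from 7.0 to 7.3 points (2.80 × 2.61). A reader might infer that the trial is underpowered in general, or that 80% needs an ICC of 0.05 or lower. Step 6 shows neither holds: at CAC 0.55 the threshold is an ICC of about 0.084. A later null result would in any case be judged on its confidence interval and on the estimated ICC and CAC, which the statistical methods section promises to report.

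**Site volume.** One might take the eligibility minimum of 20 patients a year as 10 per period, which gives 68.6%. A minimum is not an expected mean, so that figure does not bear on the claim.

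**Conclusion.** The concern holds in a limited form. In the scenario the protocol names, and with its stated 15 patients per hospital-period, 33 hospitals in batches of 12, 10 and 11 have about 76.5% power. That is about 3.5 points below the stated floor of 80%. With 2400 patients it is about 72.6%, although that also changes the cluster-period size and reflects a separate mismatch between 2400 and 15 per period.

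The result rests on equal cluster-period sizes, a normal approximation, the average of the two binomial variances, and near-balanced allocation within batches. No allocation with at least one hospital in every sequence lifts it to 80%. Unequal cluster-period sizes would usually lower power further.

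It does not follow that the design is unsound or that more hospitals are needed. This is a correction to a stated figure that should be made; it does not threaten the trial.

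**What to change.** In the sample size section, replace the batched-variant sentence with power for the trial as it stands:

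- Give the hospital count and batch sizes (33, as 12/10/11) and the cluster-period size used.
- State about 76% at ICC 0.1 and CAC 0.55 with 15 per hospital-period, and about 73% at 2400 patients. Say which of the two patient numbers is expected.
- State where 80% holds at 15 per period: at ICC 0.1 when CAC is about 0.7 or more (80.2%), or at CAC 0.55 when ICC is about 0.084 or lower (88.5% at 0.05).
- Keep the 84%, labelled as belonging to the superseded 40-hospital design.

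If the figure above 80% was computed for a different number of hospitals, say so and give that number. The cost is a change of wording and a less favourable stated power; enrolment, design and analysis are untouched.

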### Recruitment {15}

Hospitals were invited to register their interest in participating in this trial via an Expression of Interest (EOI) process. An EOI form was initially distributed through professional networks and organisations such as the Australian & New Zealand Hepatic, Pancreatic and Biliary Association (ANZHPBA), the Abdominal Radiology Group Australia and New Zealand (ARGANZ) of the Royal Australian and New Zealand College of Radiologists (RANZCR), the Australasian Gastro-intestinal Trial Group (AGITG), and the Royal Australasian College of Surgeons (RACS). Eligible hospitals that submitted an EOI and agreed to participate were further contacted with the help and coordination from local surgeons and/or radiologists (many of whom acted as site PIs or AIs). Relevant ethics and research governance applications were prepared and submitted, and after the site governance authorisation has been granted for the trial to be conducted at a specific site, all patients who undergo radiological staging of PDAC at each participating hospital will be included in the study. Individual clinicians will list patients for MDM discussion at the participating sites as per usual care.

## Assignment of interventions: allocation

### Sequence generation {16a}

Hospitals will start the study in three batches. In each batch, hospitals will be randomised to one of the sequences of the stepped wedge design, as illustrated in Table 2. Randomisation is via computer-generated random numbers generated by the trial statistician. This sequence was sent to a researcher otherwise uninvolved with the trial.

### Concealment mechanism {16b}

The otherwise uninvolved researcher created ID numbers for each hospital, and the trial statistician was unaware of the link between ID numbers and hospitals. This uninvolved researcher then sent the sequence of hospitals to the first author. Hospitals will be informed that they will be switching to synoptic reporting about 1 month prior to their allocated switch time.

### Implementation {16c}

The trial statistician generated the allocation sequence. Since this is a cluster randomized trial with a waiver of consent, individual patient recruitment is not taking place.

